#### Exclusion criteria

Exclusion criteria include: Recent abnormal esophagogastroduodenoscopy or evidence of any organic diseases affecting gastrointestinal tract (e.g. erosive esophagitis, peptic ulcer, dysplasia, mucosa-associated, lymphoid tissue lymphoma, esophageal cancer, or gastric cancer). Signs of irritable bowel syndrome. Serious symptoms, including weight loss, black or tarry stool, or dysphagia. Cardiac, pulmonary, hepatic or renal disease, or mental illness. Gastrointestinal surgery, except for appendectomy performed more than 6 monthsprior to the study. Women who are pregnant or breastfeeding. Individuals taking drugs that could affect the gastrointestinal tract. A minimum washout period of 2 weeks is required before participating in the trial. Participation in another clinical trial within 1 month of this trial. Positive for human immunodeficiency virus infection. Individuals taking herbal medicine or an oriental remedy for dyspepsia, or drugs that are considered inappropriate for this study. Difficulties in attending the trial (e.g., paralysis, serious mental illness, dementia, drug addiction, time constraints, severe disorders of vision or hearing, illiteracy, etc.). Patients who have severe depression (more than 24 points in Beck Depression Inventory) will be excluded [11]. Other issues that could interfere with acupuncture treatment (e.g., clotting disorders, leukopenia, pacemaker, epilepsy, or anticoagulant therapy).

### Recruitment procedures

Participants will be recruited in hospital outpatient clinics; by banner advertisements placed on the notice boards in the local communities; advertisements in the local newspaper, bus, and subway stations; and advertisements on web sites visited by patients with digestive diseases. Patients interested in participating will contact the Clinical Research Coordinator for further information. Patients will be screened for eligibility by a telephone interview and scheduled for an initial visit for serologic test including white blood cell, hemoglobin, hematocrit, platelet, aspartate transaminase, alanine transaminase, blood urea nitrogen, and creatinine test. After being fully informed about the procedures and risks, and given sufficient time to make a decision, participants who are deemed eligible will provide written, informed consent. Participants have the right to withdraw from the trial at any time during the study period.

### Randomization, allocation concealment, and blinding

After participants have completed a baseline evaluation, they will be randomized to two groups: the augmented group and the limited group. The randomization will be carried out using random number lists, created in accordance with the PROC PLAN of SAS 9.4 (SAS Institute Inc., Cary, NC, USA) by an independent statistician. The acupuncture practitioner will be unaware of the allocation until opening an opaque, sealed envelope. Participants will not be informed that we are studying the patient-practitioner interaction. They will be told the study is "Acupuncture for the treatment of functional dyspepsia: An international multicenter trial." Participants will be informed of the purpose of the study in a debriefing session at the end of the study. The Clinical Research Coordinator evaluating the variables will be blinded to the allocation.

### Intervention

#### Augmented group

The augmented group intervention contains two of components. First, a holistic assessment based on Traditional Korean Medicine in which the practitioner will discuss physical, psycho-emotional, social, and existential/spiritual parameters. Second, specific context enhancements, such as warmth and support, empathic attention, attentive listening, thoughtful silence, shared explanation and exploration of meaning, positive expectation, and therapeutic touch, including pulse and tongue evaluation. Many of these context enhancements are included in acupuncture practitioners’ style of treatment.

In the augmented interaction group, in addition to questions about FD symptoms, the practitioner will explore the emotional experience of FD, and the meaning of FD as a condition experienced by the patient. As part of the interview process, the practitioner will engage in the seven specific enhancements. The use of these specific enhancements will occur at different times, in as natural a way as possible.

#### Limited group

The limited group will be conducted like a serious scientific encounter. It is meant to provide limited patient-practitioner interaction, and to evaluate the impact of the intervention in isolation from other context effects. Palpation of the pulse and abdominal examination will not be done. Practitioners will not explore the emotional experience, or the meaning of the illness. Furthermore, practitioners will not engage in any of the context enhancements, but will engage the patient as naturally as possible with a “matter of fact” and “to-the-point” demeanor.

The practitioner will read a script to the patient explaining that the patient-practitioner interaction must to be kept to a minimum because of the scientific nature of a randomized controlled trial. Subsequent treatment sessions will be performed within the limits defined in the first session, thus the context will remain restricted. The acupuncture treatment will take 20 min and will involve no additional communication between practitioner and patient.

While maintaining a personable and reassuring demeanor, the practitioner will avoid engaging in education or reframing of the participant’s pain or condition, and will avoid any verbal interaction, other than that necessary to evaluate the participant’s initial condition, change, and progress. The practitioner will strive to maintain a natural and comfortable interaction with the patient, as to not compromise the validity of the treatment. The differences between the augmented and limited groups are detailed in Table 1.

**Table 1 Tab1:** Guideline for augmented and limited interaction context

Augmented Interaction context	Limited Interaction context
1. Warm, Friendly Style	1. Neutral, Impersonal Style
- Shake hands - Thank patient for participation in study - Frequent use of patient’s name. - Sit face to face, not separated by a desk - Appropriate smiling - Appropriate use of humor	- Do not initiate hand shaking - Do not thank patient for participation - Infrequent use of patient’s name - Sit separated by desk - Limit smiling - Avoid humor
2. Attentive	2. Distracted
- Frequent eye contact - Leans in at appropriate points - Appropriate use of head nods - Limited use of computer or clipboard	- Infrequent eye contact - Bodily posture conveys distance - Minimal use of head nods - Frequent use of computer or clipboard
3. Active Listening	3. Minimal Active Listening
- Open-ended questions that emphasize patient’s experience of illness - Avoid interrupting patient - Patient speaks more than clinician - Allow some silence for contemplation - Reflections - Clarifications	- Closed-ended questions (yes or no) - Tightly focused on review of systems - Interrupt patient to keep to script - Clinician does most of the talking - Fill silences quickly - Avoid reflections - Avoid clarifications
4. Personalized Content	4. Generic Content
- The clinician will encourage the patient to speak for the majority of the time - The clinician’s explanation of the illness and treatment will be personalized, using the patient’s own words wherever possible	- The clinician will dominate the interview, speaking for the majority of the time - The clinician’s explanation of the illness and treatment will be generic with no personalization for the patient
5. Empathic Connection	5. Reduced Empathy and Connection
- Partnership (We’ll work together) - Empathy (That must have been painful) - Validate emotions	- No expression of partnership - No empathy expression (but not callousness) - Avoid emotional content
6. Mirroring	6. No Mirroring
- Mirror patient’s prosody (volume, pace, intonation) - Avoid medical jargon - Use vocabulary familiar to patient	- No effort at mirroring patient’s prosody - Use medical jargon - No effort to use vocabulary familiar to patient

#### Treatment fidelity

In order to evaluate compliance with the protocol and treatment fidelity, the first acupuncture session for all subjects will be videotaped. Ten percent (10%) of videotapes will be randomly reviewed to assure that the practitioners in the augmented and limited groups follow the standard operating procedure. Patients will be made aware of the recording as part of the informed consent process, and only the interview will be recorded. Participants will be told that the purpose of the recording is to assure practitioners compliance with the protocol. Videotaping of treatment will not be performed, and the practitioner will assure that the video is turned off when the acupuncture treatment starts.

#### Acupuncture treatment

Acupuncture will be applied in the same manner in both groups. A total of 12 acupoints (Hegu [LI 4], Zusanli [ST 36], Taichong [LR 3], Quze [PC 3], Gongsun [SP 4] and Liangqiu [ST 34] bilaterally) will be used twice weekly for 4 week (8 sessions). Acupuncture will be performed as follows. The acupuncture needle will be applied to the participant’s skin. Then, after turning on the timer, the acupuncture needles will be rotated right and left for 3 s at each acupoint (total 12 acupoints). After 20 min, the timer is turned off, and the acupuncture needles will be rotated right and left for another 3 s at each acupoint, and then the acupuncture needles will be removed.

Detailed information regarding the acupuncture rationale is described in the revised STandards for Reporting Interventions in Clinical Trials of Acupuncture (STRICTA) [12] shown in Table 2.

**Table 2 Tab2:** Acupuncture treatment details based on the STRICTA (Macpherson H et al., [12]) checklist

Item	Detail
1. Acupuncture rationale	1a) Style of acupuncture - Manual acupuncture based on traditional meridian theory.
	1b) Reasoning for treatment provided, based on historical context, literature sources, and/or consensus methods, with references where appropriate - Based on the traditional meridian theory, clinical experience, and consensus by the experts in acupuncture and FD.
	1c) Extent to which treatment was varied - No additional acupoints allowed.
2. Details of needling	2a) Number of needle insertions per subject per session (mean and range where relevant) - Fixed 12 acupoints.
	2b) Names (or location if no standard name) of points used (uni/bilateral) - LI 4, ST36, LR3, PC3, SP4 and ST34 (bilateral)
	2c) Depth of insertion, based on a specified unit of measurement, or on a particular tissue level - From 5 to 30 mm.
	2d) Response sought (e.g. de qi or muscle twitch response) - ‘De qi’ sensation
	2e) Needle stimulation (e.g. manual, electrical) - Manual acupuncture
	2f) Needle retention time - Twenty minutes.
	2g) Needle type (diameter, length, and manufacturer or material) - A sterilized stainless steel needle (0.25 × 40 mm, DONGBANG ACUPUNCTURE INC., Ungcheon, Boryeong, Korea).
3. Treatment regimen	3a) Number of treatment sessions - Eight sessions.
	3b) Frequency and duration of treatment sessions - Twice weekly for 4 weeks, 20 min for each session.
4. Other components of treatment	4a) Details of other interventions administered to the acupuncture group (e.g. moxibustion, cupping, herbs, exercises, lifestyle advice) - Advice for lifestyle habit included and no other interventions during the study allowed.
	4b) Setting and context of treatment, including instructions to practitioners, and information and explanations to patients - Participants will be informed that the acupuncture treatment is based on traditional Korean Medicine and previous studies on clinical trial.
5. Practitioner background	5) Description of participating acupuncturists (qualification or professional affiliation, years in acupuncture practice, other relevant experience) - Korean Medicine Doctors who have license and at least 2 years of experience of treating gastrointestinal diseases. They have studied acupuncture for more than 10 years and graduated university of Korean medicine. To ensure providing identical treatments, they finished 10 h of training and simulated the protocol.
6. Control or comparator interventions	6a) Rationale for the control or comparator in the context of the research question, with sources that justify this choice - No control intervention
	6b) Precise description of the control or comparator. If sham acupuncture or any other type of acupuncture-like control is used, provide details as for Items 1 to 3 above.

*LI* Large intestine meridian, *ST* Stomach meridian, *LR* Liver meridian, *PC* Pericardium meridian, *SP* Spleen meridian

### Outcome measurements

#### Primary outcome

##### Proportion of responder

Proportion of responder (PR) will be used to evaluate the proportion of patients who showed alleviation of FD symptoms, with relief of stomach pain or discomfort. PR is defined as the proportion of participants who answer “yes” to the adequate relief question more than half the time during the treatment period. The adequate relief question is, "After the last visit, have you had adequate relief of your stomach pain or discomfort?" The adequate relief question will be asked at every visit, starting with the second visit. PR will be calculated for the 4-week period. This indicator has been applied in several studies with functional intestinal diseases [9, 13, 14].

#### Secondary outcomes

##### Nepean dyspepsia index

The Nepean Dyspepsia Index (NDI) was validated by Talley et al. [15] and is a reliable index to measure the degree of dyspeptic symptoms, and the quality of life. Lee et al. developed the Korean version of the NDI [16]. Although, the NDI is composed of two categories, in this study, we will use only the symptom-based questions covering the period, severity, and degree of distress of 15 symptoms.

##### Short form 36-item health survey

The Short Form 36-item Health Survey (SF-36) is a self-report health status measure, that provides information about the overall health of the individual, and includes physical, mental, and social health [17]. The Korean version of SF-36 has undergone comprehensive psychometric evaluation of reliability and validity [18].

##### The state-trait anxiety inventory

The State-Trait Anxiety Inventory (STAI) [19] investigates anxiety as a psychological factor. The STAI is a questionnaire composed of the following 40 items evaluated using a 4-point Likert scale: 20 items evaluate the state of anxiety (anxiety triggered by a specific event) and 20 items identify the trait of anxiety (anxiety derived from personal characteristics). Higher scores indicate more severe anxiety. Anxiety has a significant correlation with dyspepsia [20, 21], and the effect of acupuncture on anxiety will be evaluated using the STAI.

##### Visual analog scale for dyspepsia

Participants will be requested to check the intensity of their abdominal discomfort on 0 to 100 numerical rating scale, with 0 representing “no discomfort” and 100 representing "the most intense discomfort he/she ever had".

##### Expectations for relief scale

This scale evaluates the degree of the patients’ expectations for the treatment. Subjects will be asked two questions, "How bothersome do you expect your dyspepsia to be at the end of treatment?" and "How much do you expect acupuncture treatment will relieve your clinical dyspepsia?" Participants will be asked to indicate their responses on a 0 to 100 numerical rating scale.

##### Massachusetts General Hospital acupuncture sensation scale

The descriptors in the “Subjective Acupuncture Sensation Scale” resulting in the Massachusetts General Hospital Acupuncture Sensation Scale (MASS) were expanded by Kong et al. [22]. The MASS includes soreness, aching, deep pressure, heaviness, fullness/distension, tingling, numbness, sharp pain, dull pain, warmth, cold, throbbing, and a blank row for subjects to describe their perceptions in their own words. Establishment of the MASS involved extensive review of the relevant literature and it is the most comprehensive assessment tool in measuring the needle sensations.

##### The consultation and relational empathy measure

The Consultation and Relational Empathy (CARE) measure was originally developed to assess empathy between doctor and patient. Mercer et al. [23] confirmed the reliability and validity. The CARE measure consists of 10 questions, and each question has six options from “poor” to “excellent” and “does not apply.”

##### Interpersonal reactivity index

Interpersonal Reactivity Index (IRI) investigates the degree of empathy defined as the "reactions of one individual to the observed experiences of another" [24]. The IRI consists of 28-items answered on a 5-point Likert scale, ranging from “Does not describe me well” to “Describes me very well.” The measure has four subscales, each containing seven different items. These subscales are: Perspective Taking, the tendency to spontaneously adopt the psychological point of view of others; Fantasy, taps the respondents’ tendencies to transpose themselves imaginatively into the feelings and actions of fictitious characters in books, movies, and plays; Empathic Concern, assesses “other-oriented” feelings of sympathy and concern for unfortunate others; and Personal Distress, measures “self-oriented” feelings of personal anxiety and unease intense interpersonal settings. Korean version of IRI was validated by Kang et al. [25].

##### Maximum tolerable volume

This outcome is recorded as part of the validated nutrient drink test [26]. It is designed to induce dyspepsia, by ingesting a standard meal. When compared to a barium meal radiograph study, it is simple, non-invasive assessment that has been widely used [27, 28]. After an overnight fast, participants will consume a canned drink (Ensure, 237 ml/can, Abbott Nutrition, Columbus, Ohio, USA), at a constant rate, until they reach the maximum level of fullness. At five-minute intervals, the subjects will verbally rate their overall fullness level, on a scale of 0 to 5 (0, threshold; 5, maximum satiety). Participants will be instructed to stop drinking when their fullness level reaches 5. The actual volume consumed is the maximum tolerable volume. Questionnaires for postprandial symptoms and intensity of abdominal discomfort will be administered 30 min after drinking. If participants cannot continue to consume the test drinks, for any reason, they can voluntarily stop at any time.

##### The pictorial representation of illness and self measure

The Pictorial Representation of Illness and Self Measure (PRISM) is a two dimensional pictorial method to assess the burden of suffering. The burden of suffering is defined as "a state of severe distress associated with events that threaten the intactness of the person." Patients illustrate their burden of suffering by the distance from “self” to an illness circle, where a shorter distance indicates a higher burden of suffering. The PRISM has been validated as a reliable method for assessing the burden of suffering in a variety of chronic diseases [29].

#### Participant timeline

The time schedule of enrollment, intervention, and assessments is summarized in Table 3.

**Table 3 Tab3:** The schedule of enrollment, intervention, and assessments

Study period	Screening Visit	Acupuncture treatment period							
Visit		v1	v2	v3	v4	v5	v6	v7	v8
Week		1	1	2	2	3	3	4	4
Patients									
Informed Consent	√								
Demographics	√								
Physical examination	√								
History Examination	√								
Dyspepsia History Examination	√								
Inclusion/Exclusion Criteria	√								
Serologic test/ Evaluation	√								
BDI	√								
Randomization	√								
Trial evaluation									
Investigation of Concomitant medication		√^*^	√^*^	√^*^	√^*^	√^*^	√^*^	√^*^	√^*^
Adverse events		√^*^	√^*^	√^*^	√^*^	√^*^	√^*^	√^*^	√^*^
Outcomes									
AR of abdominal pain & discomfort			√^*^	√^*^	√^*^	√^*^	√^*^	√^*^	√^*^
VAS for dyspepsia	√	√^*^							√^†^
Expectations for Relief Scale		√^*^			√^*^				√^*^
MASS		√^†^	√^†^	√^†^	√^†^	√^†^	√^†^	√^†^	√^†^
The CARE measure		√^†^							√^†^
IRI		√^†^							√^†^
NDI		√^*^							√^†^
SF-36		√^*^							√^†^
STAI		√^*^							√^†^
PRISM		√^*^							√^†^
Nutrition drink test		√^*^							√^†^
Intervention									
Acupuncture treatment		√	√	√	√	√	√	√	√

^*^, conducted before acupuncture treatment; ^†^, conducted after acupuncture treatment; BDI, Beck Depression Inventory; *AR* Adequate Relief, *VAS* Visual analog scale, *MASS* Massachusetts General Hospital Acupuncture Sensation Scale, *CARE* Consultation and Relational Empathy, *IRI* Interpersonal Reactivty Index, *NDI* Nepean Dyspepsia Index, *SF-36* Short Form 36-item Health Survey, *STAI* State-Trait Anxiety Inventory, *PRISM* Pictorial Representation of Illness and Self Measure

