## Methods

### Design

This study is planned as a multicenter, randomized controlled, patient/assessor-blinded, clinical trial to investigate the effect of two different patient-practitioner interactions on symptoms, and quality of life, of patients with functional dyspepsia. This study will be conducted in Kyung Hee University Hospital at Gangdong, Kyung Hee University Medical Center (Seoul, Republic of Korea), and the Massachusetts General Hospital (Boston, MA, USA), from January 2017 to May 2018. Participants will be randomized in a 1:1 fashion to receive either an augmented or limited medical visit. All participants will be treated for functional dyspepsia by acupuncture for 4 weeks (8 sessions). Symptoms and quality of life will be measured by questionnaires. The practitioner will discuss patient problems, including dyspeptic symptoms, at each visit in either the augmented or limited format. The initial visit will be video recorded after obtaining the participants’ consent. The Clinical Trial Institutional Review Board (IRB) of Kyung Hee University Hospital at Gangdong (No. KHNMCOH 2016–04–007-001), Kyung Hee University Medical Center (No. KOMCIRB – 150,914 – HR-040), and Massachusetts General Hospital (No. 2016P001981/PHS) have approved the study. The study will be carried out in accordance with the standards of the International Committee on Harmonization on Good Clinical Practice, and the revised version of the Declaration of Helsinki. This study has been registered under the identifier No. KCT0002229 at CRIS (http://cris.nih.go.kr). Figure 1 provides a study flow chart.

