### Safety

Adverse events related to acupuncture treatment, including swelling, pain, bruising at the insertion site, discomfort, and dizziness will be assessed and recorded by Clinical Research Coordinator. Research physicians will manage adverse events, and the principle investigator will be notified. In the event of serious adverse events, the IRB and the sponsor will be notified within 24 h, regardless of causality. The principle investigator has the right terminate the study if serious adverse events occur.

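### No adverse-event check is scheduled after the eighth acupuncture session or the final nutrient drink test, because every check in Table 3 precedes needling and no visit follows v8

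*Protocol article*

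**What the plan says.** Table 3 (Participant timeline) has a row headed "Adverse events" with a tick at each of v1 to v8. Each tick carries the asterisk, defined under the table as "conducted before acupuncture treatment". The last column is v8, in week 4.

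The same table has a second mark, the dagger, defined as "conducted after acupuncture treatment". At v8 it is used for nine items: VAS, MASS, CARE, IRI, NDI, SF-36, STAI, PRISM and the nutrient drink test. It is not used in the adverse-event row at any visit.

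The Safety section says: "Adverse events related to acupuncture treatment, including swelling, pain, bruising at the insertion site, discomfort, and dizziness will be assessed and recorded". It assigns this to the Clinical Research Coordinator but gives neither the time of assessment nor the end of the collection period. For serious events it says: "In the event of serious adverse events, the IRB and the sponsor will be notified within 24 h, regardless of causality".

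**The concern.** The reactions that the Safety section lists arise during or after needling. A check made before a session can only look back on earlier sessions. The check at v1 therefore cannot record any needling reaction, and the check at v8 cannot record a reaction to session 8.

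The final nutrient drink test has the same problem. At v8 it comes after acupuncture and so after the last scheduled safety check, whereas the drink test at v1 is followed by the check at v2.

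At stake is the completeness of the trial's account of acupuncture-related events. A per-session rate that divided the recorded events by all eight sessions would include sessions that no scheduled check followed.

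**Working it through.** The plan states no figure on this point, so there is none to reproduce. The check is a count from Table 3.

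**Inputs**
- Planned participants: 88 (Abstract; Participants; Sample size calculation).
- Sessions per participant: 8, one at each of v1 to v8 (Design; Table 3).
- Adverse-event checks: one per visit, each before that visit's needling (Table 3).
- Later scheduled visits: none (Table 3).

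**Rule.** Session k is covered if at least one scheduled check takes place after it. Because check k precedes session k, session k is covered only by a check at v(k+1) or later.

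**Result per participant**
- Sessions 1 to 7 are covered by the checks at v2 to v8.
- Session 8 would need a check at a ninth visit, and there is none.
- Covered: 7 of 8 sessions. Not covered: 1 of 8 = 12.5%.

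**Result for the trial, with full attendance**
- Planned sessions: 88 × 8 = 704.
- Followed by a scheduled check: 88 × 7 = 616.
- Not followed by one: 704 − 616 = 88, and 88/704 = 12.5%.
- Final drink tests not followed by one: 88 of 88 × 2 = 176 tests, or half.

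**What this can mean for event counts.** Let r be the expected number of needling events per session, the same at every session. The expected total per participant is 8r. If nothing from session 8 is reported outside the schedule, 7r is recorded. The share missed is (8r − 7r)/8r = 1/8 = 12.5%. Any unscheduled reporting makes it smaller.

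**Effect on the proportion of participants with any event.** This is smaller. The documents give no event rate, so two per-session risks are assumed, with independent sessions and no capture after session 8. The recorded proportion is 1 − (1 − p)^7 and the true one is 1 − (1 − p)^8.

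| Assumed p | Recorded | True | Relative shortfall |
|---|---|---|---|
| 5% | 30.2% | 33.7% | about 10% |
| 20% | 79.0% | 83.2% | about 5% |

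**The case against.** A reader might infer from Table 3 that events after session 8 are never ascertained and that the reported counts will be one eighth too low. The documents do not support either statement. The Safety section says that acupuncture-related events "will be assessed and recorded by Clinical Research Coordinator" and does not confine this to the times in Table 3. Serious events must be notified within 24 hours, with no link to a visit. The one-eighth figure needs a constant rate and no reporting outside the schedule, and the protocol states neither. Nor does it commit to a per-session rate with eight sessions as the denominator. This part of the objection stands and limits the point to scheduled checks and non-serious events.

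Participants also remain on site after the last needling. MASS asks about soreness, aching and pain and has a free-text row. After the drink test, "Questionnaires for postprandial symptoms and intensity of abdominal discomfort will be administered 30 min after drinking". Staff may well notice an immediate reaction. But these are outcome measures and not safety records, and bruising, swelling and dizziness are not among the MASS descriptors.

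The drink test is the weaker half of the point. It is meant to provoke dyspepsia, and the Safety section's list concerns acupuncture. Symptoms that the test is intended to induce need not count as adverse events. What stands is only that no scheduled check follows the final test.

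It can also be said that Table 3 is a summary and that a journal article leaves the length of the reporting period to the full protocol. That would answer a complaint that the period is not given. It does not answer this point, because Table 3 does fix the timing: it assigns a before or after mark row by row and puts adverse events before needling at the very visit where nine other items come after. The debriefing session at the end of the study is not in Table 3, and the only purpose given for it is to disclose the study's aim.

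**Conclusion.** The point holds in a limited form. Under Table 3 no adverse-event check is scheduled after session 8 (88 of 704 planned sessions, 12.5%, with full attendance) or after the final nutrient drink test. Non-serious events from that session depend on unscheduled or spontaneous reporting.

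The loss of needling events is at most about one eighth, on the assumptions of full attendance, a constant per-session rate and no unscheduled reporting. It could be close to nil if the coordinator records events at the end of v8 anyway.

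Both arms have the same needling and the same schedule, so the gap gives no evident bias between arms and does not touch the primary outcome. It is worth correcting because the safety counts would be more complete at almost no cost.

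**What to change.** - In Table 3, mark the v8 adverse-event entry as both before and after acupuncture. Place the second check at the end of v8, after the questionnaires given 30 minutes after the drink.
- Reconcile Table 3 with the Safety section by stating there when adverse-event collection ends.
- Keep the v1 entry as adverse-event collection since consent. It should not be relabelled as a baseline record, because consent, blood sampling and the v1 drink test all come before the first needling.
- If the schedule stays as it is, any per-session event rate should count only sessions followed by a check, which is 7 per completer.
- A telephone check after v8 is optional. Without it, events that appear only after the participant has left v8 still rest on spontaneous reporting.

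The cost is one more form entry at a visit where post-treatment forms are already completed, plus one sentence in the Safety section. Treatment, sample size and the efficacy analysis do not change.
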